### **Module 1**

Question 1: Do you think you have had a uveitis worsening or disease recurrence (relapse) in the past month?

Yes, no or uncertain. If yes, specify which eye and duration.

Question 2: Have you ever experienced newly occurred eye redness in the past month?

Yes, no or uncertain. If yes, specify which eye and duration.

Question 3: Have you ever experienced newly occurred eye pain in the past month?

Yes, no or uncertain. If yes, specify which eye and duration.

Question 4: Have you ever experienced new blurred vision or decreased vision in the past month?

Yes, no or uncertain. If yes, specify which eye and duration.

Question 5: Have you ever experienced newly occurred light sensitivity in the past month?

Yes, no or uncertain. If yes, specify which eye and duration.

Question 6: Have you ever had newly occurred dark, floating spots in your field of vision (floaters, specks or moving clouds in your vision) in the past month?

Yes, no or uncertain. If yes, specify which eye and duration.

Question 7: Have you ever experienced other ocular or systemic symptoms in the past month?

Yes, no or uncertain. If yes, specify where and duration.

Question 8: Have you already been received any dose of COVID-19 vaccination?

Yes or no. If no, jump to Question 14.

Question 9: Which COVID-19 vaccine did you get?

Sinovac (CoronaVac), Sinopharm, ZFSW Biologics Company, others (specifically), or uncertain.

Question 10: How many doses of COVID-19 vaccines have you already been received?

One, two, three or more (specific numbers).

Question 11: When did you get each dose of COVID-19 vaccines?

Participants will be asked to provide the specific date as far as possible.

Question 12: Have you finished all required doses of COVID-19 vaccines?

Yes or no. If the answer is no, continue on Question 13, otherwise finished.

Question 13: When do you plan to get the next vaccine?

Participants will be asked to provide the specific date as far as possible. If participants answer they no longer intend to get the next vaccine, specific reasons should be provided. Questions finished.

Question 14: Why did not you get vaccinated?

Patients will be asked to provide the reason for not having COVID-19 vaccination. Not willing to get vaccination, willing to get vaccination but having not yet gone to the vaccination site (specific reasons for not yet gone to the vaccination site required), having gone to the vaccination site but refused due to the lack of vaccines, having gone to the vaccination site but refused due to contraindication, other reasons (specifically). After completing this question, all participants will be encouraged to go to get vaccination as soon as possible on the phone, although they might have shown

their unwillingness to get one or they might have tried but failed.

At the end of phone call, if the patient answer yes to any of questions 1 to 7 in the Module 1, the patient will be instructed to come back to study site to complete in-person clinic visit for further evaluation and examination. Alternatively, the patient will also be allowed to go to local hospitals for evaluation and examination, but the patient need to send back the copies of all medical notes, records, laboratory or auxiliary examination reports from the local hospitals. **Participants will receive best medical judgment and proper treatment for worsening of the ocular or systemic conditions, including but not limited to step-up treatment, treatment interruptions even hospitalization. Nasopharyngeal swabs for RT-PCR testing of SARS-COV-2 will be performed on cases of hospitalization.** No matter where the evaluation is completed, patients will be instructed to undergo three mandatory ocular assessments, including **best-corrected visual acuity testing, slit-lamp biomicroscopy and ophthalmoscopy.** Mandatory materials send back from local hospitals include the medical record written by the attending doctor with signature and the prescription of that clinic visit. An adjudication committee who are unaware of group assignment will independently determine the endpoint according to these medical records from our study site or the local hospitals. **If clinically-confirmed uveitis worsening occurs, participants will be recommended to postpone subsequent vaccination until uveitis remission.**

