#### **5.4 Baseline Assessments**

The Baseline visit becomes time-point zero from which all other visit dates are calculated. The Screening and the Baseline can be performed on the same day. Considering the pragmatic study design, to ensure a rapid enrollment and data collection for a broad range of participants, baseline clinical characteristics and medical history can be either reported by patients or retrieved by means of a study site-specific query of the health record. Pre-specific baseline data include the date of

birth, gender, ethnic group, height, weight, presence of hypertension, diabetes, coronary heart disease, malignancies, type of uveitis (anterior, intermediate, posterior or panuveitis), specific uveitis diagnosis, affected eye (right, left or both), duration of uveitis, number of flares in the past 12 month, best corrected visual acuity logMAR score, and intraocular pressure.

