## **5.6 Follow-Up**

Routine follow-up encounters will then occur every month. Participants will complete trial visits primarily by telephone calls from the call center. However, all participants will need to complete an in-person clinic visit on the end of three months since baseline.

On phone call, patients will be asked to answer the following predetermined questions according to their randomization assignment. **Module 1** will be subjected to those in

prompt vaccination group, and **Module 2** will be subjected to those in deferred vaccination group.

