## **Module 2**

Question 1: Do you think you have had a uveitis worsening or disease recurrence (relapse) in the past month?

Yes, no or uncertain. If yes, specify which eye and duration.

Question 2: Have you ever experienced newly occurred eye redness in the past month?

Yes, no or uncertain. If yes, specify which eye and duration.

Question 3: Have you ever experienced newly occurred eye pain in the past month?

Yes, no or uncertain. If yes, specify which eye and duration.

Question 4: Have you ever experienced new blurred vision or decreased vision in the past month?

Yes, no or uncertain. If yes, specify which eye and duration.

Question 5: Have you ever experienced newly occurred light sensitivity in the past month?

Yes, no or uncertain. If yes, specify which eye and duration.

Question 6: Have you ever had newly occurred dark, floating spots in your field of vision (floaters, specks or moving clouds in your vision) in the past month?

Yes, no or uncertain. If yes, specify which eye and duration.

Question 7: Have you ever experienced other ocular or systemic symptoms in the past month?

Yes, no or uncertain. If yes, specify where and duration.

Question 8: Have you been disease-free and discontinuing uveitis treatment for 3 months?

Yes or no. If yes, jump to Question 15.

Question 9: Have you already been received any dose of COVID-19 vaccination?

Yes or no. If no, participants will be recommended to keep away from getting vaccination at present and the conversation will be finished, otherwise continue on Question 10.

Question 10: Which COVID-19 vaccine did you get?

Sinovac (CoronaVac), Sinopharm, ZFSW Biologics Company, others (specifically), or uncertain.

Question 11: How many doses of COVID-19 vaccines have you already been received?

One, two, three or more (specific numbers).

Question 12: When did you get each dose of COVID-19 vaccines?

Participants will be asked to provide the specific date as far as possible.

Question 13: Have you finished all required doses of COVID-19 vaccines?

Yes or no. If the answer is no, continue on Question 14, otherwise finished.

Question 14: When do you plan to get the next vaccine?

Participants will be asked to provide their plan on specific date as far as possible. If participants answer they no longer intend to get the next vaccine, specific reasons should be provided. Questions finished.

Question 15: Have you already been received any dose of COVID-19 vaccination?

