## **5.8    Withdrawn and Lost to Follow-up**

Subjects have the right to withdraw from the trial at any time and for any reason, without providing a reason. The investigator has the right to withdraw participants from the study and abandon assigned intervention strategies in the event of inter-current illness, adverse events, protocol violations or other reasons.

If the subject withdraws from the trial, efforts will be made to continue to obtain follow-up data, with the permission of the subject. They will be given appropriate treatment, but will not continue with scheduled study follow-ups unless they allow it.

Subjects will also be considered to have been withdrawn if they declare they are no longer interested in further participation, or have died. If the death is considered to be related to the vaccines, the subject will be declared serious adverse event, rather than withdrawn.

Missing a phone call or visit does not necessarily mean that a patient has been withdrawn from the study. For these subjects, efforts will be made to contact them and bring them back as soon as possible.

For those subjects fail to response the contact or to attend study visits without stating

an intention to withdraw from the study, the Investigator should contact the subject through telephone calls as soon as possible. The investigator will attempt to contact them for at least three times at each scheduled visit. If contact cannot be established up to the end of the trial, the subject should be considered as “lost to follow-up” on the date of last contact.

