## **5.10 Study Schedule Overview**

|                                            | Screenin
g/Baselin
e | Month 1
(phone
call) | Month 2
(phone
call) | Month 3
(in
person) | End trial
month
after
Month 3
(phone
call) | Post-sym
ptom
visit (our
study
site or
local
hospital) | Unsched
uled visit
(in
person) |
|--------------------------------------------|----------------------------|----------------------------|----------------------------|---------------------------|-----------------------------------------------------------|--------------------------------------------------------------------------|-----------------------------------------|
| Visit window (day)                         | 0                          | ±7                         | ±7                         | ±14                       | ±7                                                        | -                                                                        | -                                       |
| Written informed consent                   | ×                          |                            |                            |                           |                                                           |                                                                          |                                         |
| Inclusion/exclusion criteria               | ×                          |                            |                            |                           |                                                           |                                                                          |                                         |
| Randomization                              | ×                          |                            |                            |                           |                                                           |                                                                          |                                         |
| General information and medical history    | ×                          |                            |                            |                           |                                                           |                                                                          |                                         |

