### 6.2 Primary Outcome

The primary outcome will be the time to symptomatic worsening over the course of 3 months of follow-up.

**Symptomatic worsening is defined if one of following newly onset symptoms occurs in at least one eye lasting for at least 2 days: eye redness, eye pain, decreased vision, light sensitivity or floaters.**

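### Symptom questions look back only one month, while the visit windows allow 44 to 51 days between contacts; a few short episodes can go unrecorded

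*Supplement*

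**What the plan says.** Protocol section 5.6 sets monthly contacts ("Routine follow-up encounters will then occur every month"). Months 1 and 2 are telephone calls and Month 3 is a clinic visit. Section 5.4 fixes the anchor: "The Baseline visit becomes time-point zero from which all other visit dates are calculated". Section 5.10 gives windows of ±7 days at Months 1 and 2 and ±14 days at Month 3, with the question module asked at all three.

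Questions 1 to 7 of Module 1 (prompt arm) and Module 2 (deferred arm) are limited to the preceding month. Examples are "Have you ever experienced newly occurred eye redness in the past month" in Module 1 and "Have you ever experienced newly occurred light sensitivity in the past month" in Module 2. A positive answer is followed by which eye (or, for Question 7, where) and the duration. No onset date is requested, although vaccination dates are. No section extends the look-back after a late or missed contact. Section 5.7 uses the same modules at unscheduled visits, and section 5.5 applies the section 5.6 questions to patient-initiated calls.

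Protocol section 6.2 defines the endpoint by symptoms alone: "Symptomatic worsening is defined if one of following newly onset symptoms occurs in at least one eye lasting for at least 2 days". SAP section 3.1 has the masked committee adjudicate from call-centre records as well as medical notes. SAP section 10 times an event at the encounter where it is reported. On missed contacts, protocol section 5.8 says: "Missing a phone call or visit does not necessarily mean that a patient has been withdrawn from the study". It then provides for efforts to bring the patient back and at least three contact attempts at each scheduled visit.

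**The concern.** The look-back has a fixed length, but the interval it should cover does not. Because target dates run from baseline and not from the last contact, an early contact followed by a late one leaves days that no scheduled question covers. An early first contact does the reverse and reaches back before randomisation.

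Both matter for an endpoint made of symptoms lasting as little as two days. An episode that starts and ends in an unasked stretch leaves nothing for the Month 3 examination to find, and the patient is carried as event-free. A symptom that came and went before randomisation could be counted as an event, since eye and duration alone do not date it. The first weeks deserve most care, because prompt-arm patients have just been advised to be vaccinated as soon as possible and the SAP hypothesis is that they worsen earlier.

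**Working it through.** The documents give no figure for coverage of follow-up, so there is none to reproduce.

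**Inputs.** Windows: protocol 5.10. Look-back: one month, taken as 30 days because the documents do not define it. Contact days: Month 1 on day 23–37, Month 2 on day 53–67, Month 3 on day 76–104.

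**Formulas.** Unasked days in an interval = max(0, interval − 30). Pre-randomisation days asked about = max(0, 30 − day of first contact).

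**Extremes, no contact missed**

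| Interval | Shortest (days) | Longest (days) | Most days unasked |
|---|---|---|---|
| Baseline to Month 1 | 23 | 37 | 7 |
| Month 1 to Month 2 | 53 − 37 = 16 | 67 − 23 = 44 | 14 |
| Month 2 to Month 3 | 76 − 67 = 9 | 104 − 53 = 51 | 21 |

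The worst single path is contacts on days 37, 53 and 104: 7 + 0 + 21 = 28 days unasked. With a 28- or 31-day month (target dates and look-back both changed), the longest intervals become 42 and 49, or 45 and 52 days; the maxima of 14 and 21 unasked days stay the same.

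**Missed contact that is not recovered.** Without Month 1, the Month 2 call on day 53–67 leaves 23–37 days unasked. Without Month 2, the interval from Month 1 to Month 3 is 39–81 days, with 9–51 unasked.

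**Before randomisation.** A Month 1 call on day 23 asks about 30 − 23 = 7 earlier days. A patient-initiated contact on day 5 would ask about 30 − 5 = 25.

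**Average.** I enumerated all combinations of whole contact days, equally likely within the windows (assumption). The mean is 8.3 unasked days, or 8.9% of follow-up. Some gap, if only of one day, occurs in 94% of combinations; a gap longer than 7 days in any one interval occurs in 36%.

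**From unasked days to lost episodes.** Suppose a patient reports any symptom still present when the look-back opens (assumption). An episode of length d is then lost only if it begins and ends in the gap, so the days on which a lost episode can start number max(0, gap − d). Averaged over the same combinations:

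| Episode length | Share of follow-up in which an episode could be lost |
|---|---|
| 0 days (limit) | 8.9% |
| 2 days | 6.0% |
| 5 days | 2.9% |
| 7 days | 1.7% |
| 14 days | 0.2% |

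With contacts within ±3, ±3 and ±7 days of target, the unasked share falls to about 4% and the 7-day figure to 0.1%.

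**Effect on power, for scale only.** Take 150 events as an assumed base. It corresponds to 0.90 event-free at 3 months in the deferred arm, hazard ratio 1.5, and 15% dropout spread over those 3 months: 1314 × (0.0924 + 0.1352)/2 ≈ 150. Power = Φ(√events × ln 1.5 / 2 − 1.96), which is 69.9% with 150 events. With the losses above it becomes 67.3% (2-day episodes), 68.7% (5-day), 69.2% (7-day) and 69.9% (14-day).

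**The case against.** The strongest reply is that unasked days are not lost events. A flare that runs into the look-back will normally be reported, so 8.9% is a zero-length limit that the two-day endpoint definition excludes. This stands, and the lost-episode table replaces the 9% as the measure of harm.

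Second, the plan has other routes to the same information. Patients are told at baseline to phone at once with any of the five endpoint symptoms, unscheduled visits repeat the module with an examination, and missed contacts trigger repeated attempts. This also stands. A reader might infer that missing Month 1 loses the first month outright, but that happens only if the catch-up in section 5.8 fails. These routes reduce the loss without removing it, because they rely on the patient volunteering or being reached, and the module then still asks about one month only.

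Third, contacts made on the target days leave no gap, and few patients treat a month as exactly 30 days. That is fair: 44 and 51 days are the extremes, the 51-day interval ends at a clinic visit, and the 94% includes trivial gaps.

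Fourth, pre-randomisation symptoms are partly screened out. Entry requires inactive disease on examination, the questions ask for newly occurred symptoms with duration, and masked adjudicators see the call records. The residual risk remains because onset is undated, but the documents do not allow it to be quantified.

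**Conclusion.** The mismatch is in the plan as written. Within the windows, up to 14 days between Months 1 and 2 and up to 21 days between Months 2 and 3 can go unasked, and more if a contact is missed and not recovered. Contacts before day 30 reach back before randomisation with no onset date to separate the two periods.

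The likely effect is small: about 6% of 2-day episodes down to 0.2% of 14-day episodes, before patient-initiated calls and unscheduled visits are credited. This rests on uniform contact days, a 30-day month and patients reporting symptoms still present when the look-back opens. The documents give no episode durations, so only a range can be stated.

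Two stronger readings are not supported. One is that 9% of events are lost, with power falling from about 70% to 66%; that treats every unasked day as a lost event. The 70% is itself an assumed base, whereas the plan states 80.0%. The other is that the comparison is biased between arms. Questions 1 to 7 and the windows are the same in both arms, and nothing in the documents shows that the loss differs between them. What is established is some loss of events and precision, avoidable at very little cost.

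**What to change.** In Questions 1 to 7 of both modules, replace the one-month look-back with *since our last completed call or visit on [date], or since you joined the study*, with the date filled in by the eCRF. Use the same wording at unscheduled visits and patient-initiated calls. Next to duration, record the symptom onset date, and state that onset before randomisation does not count as an event.

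The cost is a script change, one date field, and somewhat longer recall for patients who missed a contact. No extra contact or examination is needed. The SAP section 10 rule that times events at the reporting encounter can stay as it is; if onset dates are to be used for timing, it needs a matching one-line change.

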### **What is the key question of our study?**

In this study, we aim to initiate a pragmatic randomized trial to investigate whether there is significant difference in outcomes of patients with an inactive uveitis (active uveitis is considered not eligible for COVID-19 vaccination) between prompt initiation of COVID-19 vaccination and deferred initiation of COVID-19 vaccination until uveitis remission.

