## **5.5 Interventions**

Interventions will take place at the Baseline visit. The Primary Treating Ophthalmologist will provide the recommendation of COVID-19 vaccination to the subject according to randomization assignment. For those randomized to the prompt vaccination, subjects will be recommended to go to vaccination site and get COVID-19 vaccination as soon as possible. Our ophthalmologic clinic does not provide the vaccination service. We will only give the recommendation to patients. For those randomized to the deferred vaccination, subjects will be recommended to get COVID-19 vaccination after the remission of uveitis. **Remission is defined as an inactive disease for 3 months after discontinuing all treatments for eye disease.** At baseline, all patients will also be educated to immediately contact us by phone call once they experience any discomfort or have any new ocular symptoms of eye redness, eye pain, decreased vision, light sensitivity or fark, floating spots. We will ask questions as prespecified in **5.6 Follow-up** on the phone call.

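### Module 1 Question 14 has the caller encourage every undosed prompt-arm participant to be vaccinated, with no exception after clinically-confirmed worsening, for which the same section advises postponement

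*Supplement*

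**What the plan says.** Protocol 2.0 section 5.6 gives the prompt arm its own call script, Module 1. Questions 1 to 7 ask about relapse and symptoms in the past month. Question 8 asks whether any dose has been received, with the routing "Yes or no. If no, jump to Question 14". Question 14 asks why the participant is still unvaccinated and then instructs: "After completing this question, all participants will be encouraged to go to get vaccination as soon as possible on the phone". The clause that follows extends this to people who have shown "their unwillingness to get one or they might have tried but failed".

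The text after Question 14 covers referral for examination and ends with a rule for confirmed cases: "If clinically-confirmed uveitis worsening occurs, participants will be recommended to postpone subsequent vaccination until uveitis remission". The same sentence stands at the end of Module 2, the deferred-arm script.

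On delivery, section 5.6 says: "Participants will complete trial visits primarily by telephone calls from the call center". Section 5.5 adds that "all patients will also be educated to immediately contact us by phone call once they experience any discomfort", and that the section 5.6 questions are then asked. The SAP does not address the script.

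**The concern.** An undosed prompt-arm participant with an earlier clinically-confirmed worsening falls under two instructions in one section: be encouraged to go for vaccination without delay, and be advised to wait for remission. Nothing in Question 14 tells the caller which prevails. The protocol names relapse as the main potential risk of participation (section 1.2), so the advice most likely to go wrong is the advice meant to limit that risk. What is at stake is participant safety and consistent delivery of the strategy, not the validity of the primary comparison.

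**Working it through.** No sample size, power or alpha figure is involved, so the check is a reading of the routing and a count from the visit schedule.

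**1. Who reaches the encouragement.** The path is Questions 1–7, then Question 8 answered no, then Question 14, then encouragement. The answers to Questions 1–7 do not alter it. The qualifiers on the encouragement (unwilling, or tried and failed) widen it; none limits it. No item asks specifically whether a worsening has been clinically confirmed.

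**2. What the postponement rule covers.** There are two readings of *subsequent vaccination*.
- *Any vaccination after the event.* An undosed participant with confirmed worsening is then covered by both instructions, and they contradict each other. The identical sentence in Module 2 favours this reading, because deferred-arm participants are asked to stay unvaccinated until remission. It does not settle it, because Module 2 also has questions for people who have been dosed.
- *Later doses only.* The contradiction then disappears, but undosed participants with confirmed worsening have no hold on vaccination, and Question 14 still urges them to go.

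Either way the script needs a change.

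**3. Whether remission could remove the problem before the next contact.** Remission requires three months of inactive disease after all eye treatment has stopped (section 5.5). Take a worsening confirmed after the Month 1 call. Using the windows in section 5.10, the longest gap from the Month 1 call (7 days early) to the Month 3 visit (14 days late) is 2 months + 7 + 14 days = 2 months and 21 days, which is under three months. Such a participant cannot be in remission at the Month 2 call or the Month 3 visit.

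**4. How often the script recurs.** Section 5.10 schedules the module at Month 1 (phone), Month 2 (phone), Month 3 (in person) and a call after Month 3.
- Scheduled runs: 4, of which 3 are by phone.
- After a Month 1 symptom report that is then confirmed: 4 − 1 = 3 later runs, of which 3 − 1 = 2 are by phone.
- Symptom call-ins (section 5.5) and unscheduled visits (section 5.7) add further runs.

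The encouragement is worded as given by phone, so the two later phone runs are the firm count.

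**5. How the protocol handles similar situations.** In Module 2 the encouragement at Question 16 is reached only after the participant reports three months disease-free and off treatment; other undosed participants are advised to stay away from vaccination for now. Section 5.6 also stops all recommendations to deferred-arm patients vaccinated before remission. Module 1 has no comparable condition.

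**6. Number affected.** It cannot be derived. The case needs someone who is undosed, has a confirmed worsening and is contacted again. The documents give neither vaccine uptake over time nor the share of symptomatic cases that are confirmed. The sample-size inputs (event-free proportion 0.90, hazard ratio 1.5) concern symptomatic worsening in whole arms and say nothing about confirmed worsening in undosed people.

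**The case against.** The strongest reply is that a specific, conditional rule placed after a general script line naturally qualifies it, so what is missing is a cross-reference rather than a safety policy. Several other points support this. Question 14 allows other reasons to be specified, so a participant told to postpone can say so. Question 1 asks about a recent worsening. No text says that callers lack the clinical record. The investigator may abandon the assigned strategy (section 5.8), may stop it after an adverse event (section 7.7), and is expected to act at once for safety even against the protocol (section 10).

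Much of this stands. It keeps the point small and makes it likely that an alert caller would do the right thing. It does not remove the point: the instruction covers everyone who reaches Question 14, whatever reason is given, and none of the discretionary powers is tied to the script. A scripted call needs the condition written into it.

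A reader might infer a stronger fault: that encouraging anyone who has just reported eye symptoms is also an error, since section 1.1 says that "active uveitis is considered not eligible for COVID-19 vaccination" and the referral for examination comes only afterwards ("At the end of phone call, if the patient answer yes to any of questions 1 to 7 in the Module 1"). The documents do not support that. Section 4.1 defines inactive disease by examination findings. Questions 1 to 6 record self-reported worsening or symptoms at any time in the past month, without the two-day minimum of the primary outcome, and the symptoms may have resolved. A yes does not establish active disease, the same call leads to an examination, and no stated rule is broken. Holding back the encouragement until records return, possibly from a local hospital, would need an extra contact and would make delivery of the prompt strategy depend on non-specific self-report. That is a debatable trade-off, and no change is asked for on it.

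**Conclusion.** The point holds for undosed prompt-arm participants with an earlier clinically-confirmed worsening who are not yet in remission. Followed literally, Question 14 reverses the section's own postponement advice at the next contact or, on the narrower reading of that advice, leaves these participants with no hold. It is a minor matter of patient safety.

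No size is claimed. That the number is small is a judgement, resting on the three conditions that must coincide. It assumes that callers follow the script as written and are given no separate instruction, which the documents neither confirm nor exclude.

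It would be wrong to infer that the primary result is biased. The analysis is by intention to treat and compares participants as randomised. The conflict also arises only after a confirmed worsening, which in the phone follow-up is normally found through a symptom report, so the primary event will often already have been counted.

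**What to change.** Amend Module 1 Question 14 so that the encouragement goes to all undosed participants except those with a clinically-confirmed worsening who have not yet reached remission. For those, the caller repeats the postponement advice. State alongside the postponement rule that it applies to a first dose as well as to later doses.

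The cost is a one-line script amendment and a check of each participant's adjudication status before the call, so confirmed events have to be passed from the adjudication committee to the call center. Information needs to flow only in that direction, so the committee's masking is not touched. No visits or examinations are added.
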